#### 5.1.3. Feasibility

Clinician adoption and penetration of completing the FH diagnostic evaluation and measuring the utility of the implementation strategy package will be measured through EHR data and semi-structured interviews. The analysis for the semi-structured interviews will follow the same structure that will be utilized for acceptability.

#### 5.1.4. Fidelity

Direct observation utilizing a checklist will occur at each clinic site after deployment of the implementation strategy package and observations of any adaptations that have been made to the process will be conducted. Guided by the framework for reporting adaptations and modifications (FRAME), we will report the following data: (1) when and how a modification was made, (2) whether the modification was planned/proactive or unplanned/reactive, (3) who decided to make the modification, (4) what is modified, (5) at what level of delivery the modification is made, (6) type or nature of context or content-level modifications, (7) the extent to which the modification is fidelity-consistent, and (8) the reasons for the modification [39].

#### 5.1.5. Sustainability

Clinician and patient participants will be surveyed to measure self-efficacy related to FH care and the institutionalization potential of the implementation strategy package. Descriptive analyses including means and standard deviations or median and inter-quartile ranges, depending on distribution, will be performed. Information collected will be reported and reviewed with the advisory board to discuss potential sustainability.

## 6. Specific Aim 4 (R33): Measure Patient-Related Outcomes after Implementation of an FH Diagnostic Evaluation Program

This aim will use the patient data collected and follow-up EHR data from subsequent FH care visits (Table 2). We hypothesize that: Service and exploratory health outcomes will be achieved more frequently by clinicians and their patients after the implementation strategy package is deployed to their clinic.

### 6.1. Data Collection and Analysis for Service and Health Outcomes

#### 6.1.1. Timeliness

For measurements looking at the time to completion of tasks, key dates will be the date of first FH notification, date of the clinic visit, and dates of supporting patient contacts such as genetic counseling and lipid specialty appointments. Visits with genetic counselors will be used to assist with the tracking of genetic testing and cascade screening of relatives. An initial visit to a lipid specialist will be used to determine the time for statin initiation, if not done at the primary care visit. The 2018 AHA/ACC cholesterol guideline will be used to define evidence-based indications and goals related to statin initiation [1]. Timeliness outcomes will be analyzed using time-to-event models, including the Cox Proportional Hazard regression model.

#### 6.1.2. Function

Data to be extracted from the FH Clinic Note and follow up assessments include the presence of a definite or probable FH diagnosis or used DLCN tool to exclude FH diagnosis, medication prescribing, medication-related side effects, lipid levels (to assess compliance with evidence-based care), genetic test ordering, return of genetic results, and initiation of cascade screening. We will use descriptive statistics and compare outcomes between intervention and control conditions every six months and with reference to the four steps.

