**Figure 2 jpm-12-00606-f002:**
[figure not shown]
FH Diagnostic Evaluation Program. ASCVD, atherosclerosis cardiovascular disease; DLCN, Dutch Lipid Clinic Network score; FH, Familial hypercholesterolemia; Clinics will move from usual care to deployment of implementation strategy package during the stepped-wedge design.

**Table 1 jpm-12-00606-t001:** Potential implementation strategy package.

Name of Strategy *	Study Specific Definition	Actor	Action	Action Target
Develop and implement tools for quality monitoring	EHR tools to order labs, record results, and document FH care	ImpT, MedT, and InfT	Use EHR to record, order, and prescribe FH Care	Service and health outcomes
Develop educational materials	Education regarding guidelines for identification and treatment of FH	MedT and InfT	Create a CME course for clinicians about FH. Explore clinician workflow and educational needs to design novel focused educational interventions integrated within clinical workflows to support evidence-based care	MedT ready to train clinicians on FH
Conduct educational outreach visits	CME educational material for FH that is presented to each clinic	MedT and clinicians	Attend CME course on FH	Improve knowledge about FH
Intervene with patients to enhance uptake and adherence	Reach out directly to patients to recommend screening for FH	Clinicians and ImpT	Letter sent to the patient. Clinician schedules patient for appointment.	Patients diagnosed with FH from those at-risk
Identify and prepare champions	Clinical lipid champions	MedT	Identify and train lipid champions	Improved performance of study metrics, reduced costs
Stage FH care delivery model scale up	Develop the timeline for the stepped-wedge rollout to primary care	Leadership team	Notify practices of roll out and schedule education	Begin the trial
Audit and provide feedback	Provide aggregate level feedback to clinics on diagnosing FH	MedT, InfT, and clinical leadership	Report back to clinicians’ aggregate level data	Improve effectiveness of the FH Diagnosis Program
Advisory board review	Clinical trial protocol	Advisory Board	Provide feedback on the clinical trial regarding protocol, generalizability and ethical issues	Protocol revision based on feedback

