* Mapped to the Expert Recommendations for Implementing Change (ERIC) compilation. Specification requirements for the implementation strategy will be tailored during aim 1 of CARE-FH. EHR, electronic health record; CME, continuing medical education; FH, familial hypercholesterolemia; ImpT, implementation science team; InfT, informatics and data science team; MedT, medical science team.

**Table 2 jpm-12-00606-t002:** Description of domains, aim, outcomes, construct measured, and data sources for phase two (R33).

Domain	Aim	Outcome	Construct Measured	Data Source
Implementation	2	**Adoption**	**FH diagnostic evaluation defined as completed of one of the following:** - Used FH clinic note to document care - Added FH diagnosis on the problem list or used DLCN tool to exclude FH diagnosis - Used the FH smart-set (i.e., ordered a genetic test for FH) - Made a referral to the lipid clinic - Initiate evidence-based lipid lowering medications	EHR, administrative data
		Penetration	Proportion of the primary care clinicians that completed the five components of the FH diagnostic evaluation compared to those that did not use it.	
	3	Acceptability	Clinician and patient satisfaction and self-efficacy with the implementation strategy package	Semi-structured interviews
		Cost	Cost to implement the implementation strategy package	Micro-costing
		Feasibility	Clinician adoption and penetration for completion of the FH diagnostic evaluation and measured utility of implementation strategy package	Semi-structured interviews and EHR data
		Fidelity	Documentation of adaptations to the FH diagnostic evaluation program	Checklist, direct observation
		Sustainability	Potential for institutionalization	Surveys, Advisory board consultation
Service	4	Timeliness	Time to: FH screen, completion of diagnostic evaluation, medication initiation	EHR, administrative data
Health		Safety	Medication-related side effects	
		Intermediate	LDL-C reduction	
		Process	Return of genetic result	
			Initiation of cascade screening	

EHR, electronic health record; FH, familial hypercholesterolemia; LDL-C, low-density lipoprotein cholesterol. Bolded is the primary outcome of the study.

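### Section 6.1.2 sources the Aim 4 outcomes from the FH Clinic Note and FH follow-up but compares intervention with control, so recording may differ by condition

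*Protocol article*

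**What the plan says.** Section 6 (Specific Aim 4) gives the data source in general terms: "This aim will use the patient data collected and follow-up EHR data from subsequent FH care visits", with a pointer to Table 2. Its hypothesis is directional: "Service and exploratory health outcomes will be achieved more frequently by clinicians and their patients after the implementation strategy package is deployed to their clinic".

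Section 6.1.2 is more specific: "Data to be extracted from the FH Clinic Note and follow up assessments include the presence of a definite or probable FH diagnosis". The same sentence covers exclusion of FH by the DLCN tool, prescribing, side effects, lipid levels, genetic test ordering, return of results and the start of cascade screening. The section then commits to descriptive statistics and to "compare outcomes between intervention and control conditions every six months and with reference to the four steps".

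Table 1 (potential package) lists as a strategy "EHR tools to order labs, record results, and document FH care". In Table 2, the first of the alternative ways to meet the primary outcome is "Used FH clinic note to document care". Table 2 also gives "EHR, administrative data" as the source on the Timeliness row. The source cells for the health rows below it are blank, probably because the cell was merged.

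**The concern.** A comparison between conditions needs outcomes that are observed in the same way in both. Section 6.1.2 names a source whose use the package is meant to increase, and gives no matching rule for a usual-care patient who has no FH note and no FH visit. Two things can follow.

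- **Absence of a note is read as absence of the event.** The package then appears to raise every recorded item, good or bad, even if the events themselves do not change. Medication-related side effects are the only Safety outcome in Table 2, so fuller recording after deployment could look like harm.
- **Patients without a note are left out.** The control group then consists of the few whose clinicians did evaluate them, set against a broader intervention group. That is selection on something the intervention affects.

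In either case the Aim 4 hypothesis could be supported in part by better documentation alone.

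**Working it through.** The plan gives no figure for this point. The article's one design figure (a 20% improvement, at least 10 clinics per region, Section 4) concerns the primary outcome and does not enter. The check is to compare the relevant statements and then illustrate how the bias behaves.

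**Step 1: the statements together**

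| Place | Content | Bearing |
|---|---|---|
| Section 6.1.2 | Source is the FH note and follow-up assessments; conditions are compared | Source may depend on exposure |
| Section 6 | Patient data collected, plus EHR data from later FH care visits; refers to Table 2 | Follow-up part is tied to FH care; pointer is to a broader source |
| Table 1 | EHR tools to document FH care are a package strategy (headed as potential) | Package promotes the source |
| Section 2.2 and Table 2 | Use of the FH note is a component of the primary outcome | Package is meant to raise note use |
| Section 3.1.3 | Study outcomes to be collected from the EHR as baseline for usual care | EHR measurement under usual care is intended |
| Section 4 | Primary and secondary outcomes collected before and after the intervention | Same intent |
| Table 2 | EHR and administrative data | Broader than 6.1.2, although the FH note is itself an EHR document |

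The last three rows show an intention to measure under usual care. They do not say how an item taken from an FH note is measured in a patient without one.

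**Step 2: which items are exposed**

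- DLCN-based classification or exclusion, side effects and cascade screening need someone to write them down. For these, recording can change while the event rate does not.
- Lipid results, prescriptions and genetic test orders can be held in routine EHR data in either period. For these, the problem arises only if extraction is restricted to the FH note or FH visits.

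**Step 3: illustration (every rate is an assumption)**

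Let p be the true event rate, equal in both conditions, and let s be the probability that an event is recorded.

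Observed rate = p × s. Spurious ratio = s(package) / s(usual care). Spurious difference = p × [s(package) − s(usual care)].

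With s(package) = 0.90 and p = 0.30:

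| s(usual care) | Observed, package | Observed, usual care | Ratio | Difference |
|---|---|---|---|---|
| 0.20 | 27% | 6% | 0.90/0.20 = 4.5 | 21 points |
| 0.50 | 27% | 15% | 0.90/0.50 = 1.8 | 12 points |
| 0.80 | 27% | 24% | 0.90/0.80 = 1.125 | 3 points |
| 0.90 | 27% | 27% | 0.90/0.90 = 1.0 | 0 points |

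At p = 0.10 the ratios are the same and the differences are 7, 4, 1 and 0 points. The ratio depends only on relative recording, and the bias vanishes when recording is equal. The formula applies to yes/no events that are scored absent when not recorded. It does not apply directly to LDL-C change on a continuous scale, where a missing source gives a missing value.

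**The case against.** The strongest reply is that the article does plan measurement under usual care. Section 3.1.3 makes collection of study outcomes from the EHR for the usual care arm a main product of Aim 1. Section 4 promises data before and after the intervention. Section 6 sends the reader to Table 2, where the source is broad. The follow-up assessments in 6.1.2 are not defined as FH-note-only, and Section 6.1.1 draws on clinic visits, genetic counselling and lipid specialty appointments. The primary outcome already counts medication initiation and lipid-clinic referral from EHR and administrative data, so such events can be detected without the note. Extraction detail and denominators are also commonly left to a full protocol or analysis plan, which is not shown here.

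Most of this stands, and it rules out a stronger reading. A reader might infer that usual care has no like-for-like measurement at all, or that usual-care statin orders and lipid panels would go uncaptured. The documents do not support that. Table 1 is headed as potential, no section says when the note becomes available or that usual-care clinicians lack it, and nothing says that patients without a note are scored as non-events. Nor do the documents establish that the narrower wording of 6.1.2 would prevail over Table 2. A very large ratio, such as the tenfold one that 50% against 5% note use would give, rests wholly on assumed rates.

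The objection does not remove the conflict within 6.1.2. The point does not rest on an omitted detail: the section names a source and, in the next sentence, a comparison for which that source is not neutral. Sections 3.1.3 and 4 state an intent without resolving this. Section 4 speaks of primary and secondary outcomes, whereas Section 6 calls the health outcomes exploratory.

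**Conclusion.** The point holds in limited form. Followed as written, Section 6.1.2 risks differential ascertainment, or selection of evaluated patients, in the Aim 4 comparison of conditions. The risk is real for DLCN-based classification or exclusion, side effects and cascade screening. It is avoidable for lipid levels, prescriptions and genetic test orders, provided these are drawn from routine records in both periods.

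The size cannot be derived from the documents. Under the recording rates assumed above it runs from no bias to a several-fold spurious ratio. That the FH note is used mainly after deployment is a reasonable inference from Table 1, not a stated fact. The primary analysis is not affected by this point. The health outcomes are exploratory and the 6.1.2 analysis is descriptive, so this is a correction worth making and not a threat to the trial's main conclusion.

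**What to change.** In Section 6.1.2, reconcile the data source with Sections 3.1.3 and 4 and with Table 2:

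1. Take every outcome that is compared between conditions from routine EHR or administrative fields: laboratory results, medication orders, and genetic test order and result records.
2. Use as denominator all patients who meet one of the four triggers in Section 2.2, whether or not an FH note or FH visit exists.
3. Apply the same time window from the trigger date in both conditions.
4. Report items found only in the FH note or at FH visits descriptively within the intervention period, with no between-condition comparison.
5. State that any side-effect comparison remains open to differential documentation even when structured fields are used, because those entries also depend on patient contact and on what clinicians record.

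The cost is a change to the extraction specification. Table 2 already names the broader source, and care is unaffected. The drawback is that structured fields lose some of the detail the note records, most of all for side effects.

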### 2.2. FH Diagnostic Evaluation Program

This program for FH care is based on the current paradigm for notification regarding actionable genetic variants in MyCode Community Health Initiative (MyCode) a research program that links exome sequence data with electronic health record (EHR) data and returns pathogenic variants in clinically actionable genes to patient-participants (Figure 2) [13,20,21,22,23,24,25]. Evaluation is triggered by the notification of the patient and primary care clinician of an actionable variant. In CARE-FH, there will be four possible triggers: the presence of an FH variant from MyCode, cascade screening of family members identified in the MyCode program, identification of patients requiring an FH workup through applications of FH screening algorithms of EHR data, or presence of an LDL-C ≥ 160 mg/dL in a child. Notification will lead to scheduling a medical appointment to complete the FH diagnostic evaluation. Successful completion of the FH diagnostic evaluation, the primary outcome of this study, will include evidence the clinician has completed evidence-based FH diagnostic evaluation and management goals. The goals are defined as completing one of the following:-Used FH clinic note to document care-Added FH diagnosis on the problem list or used the Dutch Lipid Clinic Network score (DLCN) tool to exclude FH diagnosis-Used the FH smart-set (i.e., ordered a genetic test for FH)-Made a referral to the lipid clinic [12]-Initiate evidence-based lipid lowering medications

A patient will be considered to have FH if they have a positive genetic test for FH or have a DLCN > 8 and probable FH with a score of 5–8. Geisinger primary care sites are divided by geographic region (Central, Northeast, Western, or Geisinger Medical Center) and into several practice types. Adult-oriented primary care clinics are staffed by internists, family practitioners, and advanced practice professionals (physician assistants and nurse practitioners). Pediatric practices provide primary care and acute care at 22 clinics.

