#### 3.1.2. Medical Science Team (MedT)

The MedT will meet monthly to accomplish the objectives outlined below.

Partner with the InfT to revise content for EHR tools in the implementation strategy package and subsequent adaptations.Finalize FH care plan for adults and children.Finalize strategy for incorporation of genetics counselors and specialty referrals into a care plan.Finalize study timeline, including the schedule and sites for rolling out the implementation strategy package.Alpha test the implementation strategy package at one adult and one pediatric practice site.

Interviews performed by the ImpT with clinicians at adult and pediatric practices will be used to refine the structure for the rollout of the implementation strategies. Strategies to increase pediatric screening rates will be developed. The alpha test will occur at one adult and one pediatric clinic at the main hospital, staffed by a member of the MedT. All tools developed for the implementation strategy package will be tested, using principles from human-centered design. The alpha test will be further informed by interactions with end users to assess workflow as part of the human-centered design activities. The main outcome of the R61 phase of the study will be successful first rollouts.

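### An unadjusted, descriptive comparison of LDL-C reduction between conditions can be biased by regression to the mean if the mix of children entering, or the capture of their follow-up values, differs between conditions

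*Protocol article*

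**What the plan says.** Section 2.2 gives four triggers for an evaluation: a MyCode variant, cascade screening of relatives, an EHR screening algorithm, and "presence of an LDL-C ≥ 160 mg/dL in a child".

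Table 2 lists "LDL-C reduction" as the intermediate health outcome under Aim 4, with no size, baseline or time window. Section 6 states the hypothesis: "Service and exploratory health outcomes will be achieved more frequently by clinicians and their patients after the implementation strategy package is deployed to their clinic". Section 6.1.2 collects "lipid levels (to assess compliance with evidence-based care", among other items, and gives the analysis: "We will use descriptive statistics and compare outcomes between intervention and control conditions every six months and with reference to the four steps".

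Other outcomes get a named model. The Aim 2 analysis section plans a generalized linear mixed model with covariates for the diagnostic evaluation rate, and Section 6.1.1 plans time-to-event models for timeliness.

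Three places bear on who is tested and what is recorded:
- Section 3.1.2: "Strategies to increase pediatric screening rates will be developed".
- Section 7: pediatric clinicians are to screen by lipid profile at ages 9 to 11, or to evaluate children found by cascade.
- Table 1: the package includes EHR tools for ordering laboratory tests, recording results and documenting FH care.

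**The concern.** The variable that brings some children in is also the variable whose fall is the outcome. A child picked because LDL-C was at or above 160 mg/dL will on average read lower next time, treated or not. A child who enters through a MyCode variant or a relative was not picked on a high reading, so no such fall is expected.

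Two features of the package could make the conditions unlike in this respect. More pediatric lipid testing can change the share of entrants selected on LDL-C, and the kind of child tested. Better tools for ordering and recording tests can change who has a follow-up value. A descriptive comparison corrects for neither. A difference in LDL-C reduction could then be reported as a health effect of the package, or a real one could be hidden.

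**Working it through.** The plan gives no LDL-C figure to reproduce. Its only sizing statement (20% improvement, at least 10 clinics per region) concerns the diagnostic evaluation rate.

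**Inputs.** From the article: the cut-off of 160 mg/dL. Assumed, because the article does not give them: LDL-C mean and SD in tested children, test-retest correlation r, and the trigger value as the starting value. No treatment effect is assumed anywhere below.

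**Step 1: fall after selection.** Expected fall = (1 − r) × SD × φ(k) / (1 − Φ(k)), with k = (160 − mean) / SD. For mean 95, SD 25, r = 0.7, k = 65/25 = 2.6 and the fall is 21.9 mg/dL. Simulation agrees with the formula and supplies the shares.

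| Mean / SD (mg/dL) | r | Mean fall (mg/dL) | Any fall | Fall of 10% or more | Fall of 30% or more |
|---|---|---|---|---|---|
| 95 / 25 | 0.7 | 21.9 | 89% | 61% | 5.5% |
| 95 / 25 | 0.9 | 7.3 | 75% | 19% | 0% |
| 100 / 30 | 0.8 | 14.2 | 79% | 44% | 2.0% |
| 110 / 35 | 0.7 | 19.7 | 78% | 53% | 9.2% |
| 110 / 35 | 0.9 | 6.6 | 67% | 24% | 0.2% |

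A separate simulation (mean 95 to 100, SD 25 to 28, 1 in 250 children with FH at mean 200, within-person CV 6% to 12%) gave falls of 6 to 19 mg/dL, with 68% to 79% reading lower. Without selection, 50% would read lower.

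**Step 2: does more screening alone create a difference?** With mean 100, SD 30 and r = 0.8, random screening was raised from 20% to 40% to 60% of children. Reductions per 10,000 children rose from 35 to 72 to 107. The share reduced stayed at 78% and the mean fall at about 14 mg/dL. The count rises, but the rate per triggered child does not.

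**Step 3: a shift in trigger mix.** Let w be the share of pediatric entrants selected on LDL-C, and suppose the others show no net fall. The spurious difference in mean reduction is (change in w) × (mean fall). For any fall it is (change in w) × (share − 0.50). For each 10 points of change in w:
- mean reduction: 0.1 × 6.6 = 0.7 to 0.1 × 21.9 = 2.2 mg/dL;
- any fall: 0.1 × (0.67 − 0.50) = 1.7 points to 0.1 × (0.89 − 0.50) = 3.9 points.

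The sign is that of the change in w, which the article does not give.

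**Step 4: a shift in who is tested within the LDL-C trigger.** Suppose one condition tests selectively (assumed mean 130) and the other universally (mean 100), with SD 30 and r = 0.8 in both. The share reduced goes from 69% to 78% and the mean fall from 9.2 to 14.2 mg/dL. Adjusting for the starting value alone does not remove this. At the same starting value, expected follow-up still differs by (1 − r) × (130 − 100) = 0.2 × 30 = 6 mg/dL.

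**Step 5: a shift in capture of follow-up.** If retesting went from 30% to 60% of triggered children (assumed) and 72% of those retested read lower, recorded reductions per triggered child would go from 0.30 × 0.72 = 22% to 0.60 × 0.72 = 43%. If only retested children form the denominator, bias arises when the kind of child retested differs.

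**The case against.** **The fall cancels.** Section 6.1.2 compares conditions; it does not look at change in triggered children alone. With the same cut-off in both, an equal fall drops out of a difference. This stands, and Step 2 shows it. A reader might infer that more screening by itself raises the rate of reductions, but it does not. Bias needs a difference in mix or follow-up. The article makes such a difference plausible without establishing it.

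**These are details for the full protocol or SAP.** Baseline, window and minimum change commonly are, and their absence is not the point here. The point is a stated method: description for this outcome, where models are named for others.

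**Direction is open.** The program also promotes cascade screening, which could lower the share of children selected on LDL-C. That stands. Children found by EHR algorithm are a further group whose selection on LDL-C the article does not describe.

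**Nothing says that one value suffices.** A reader might infer entry on a single unconfirmed value. The article mentions no repeat test, but it does not exclude one. Little depends on this: with a second value at or above 160 and the mean of the two as baseline, the same assumptions still give a mean fall of 3.7 to 13.9 mg/dL, with 61% to 80% reduced.

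**Counting any fall as success is a reading of the text.** The hypothesis in Section 6 covers all service and health outcomes together, and lipid levels are collected to assess compliance. So a claim that untreated falls dilute a true effect is too strong: an equal fall leaves a difference in mean reduction unchanged. Dilution arises only if the outcome is any fall at all.

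**Conclusion.** The point holds as a limited weakness of a stated analysis. Selection at 160 mg/dL produces an untreated mean fall of about 6 to 22 mg/dL, with about 67% to 89% of children showing some fall, under assumed distributions and reliability. The planned unadjusted comparison is safe only if entrant mix and follow-up are alike in both conditions. The package is built to change testing and recording, so that cannot be taken for granted.

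The size and sign of any bias cannot be fixed from the article. A reader might put it at 7 to 12 points by supposing that LDL-triggered children rise from 30% to 70% of pediatric entrants: 0.4 × (0.68 − 0.50) = 7 points, and 0.4 × (0.79 − 0.50) = 12 points. Neither share is in the article, so those figures illustrate and do not estimate.

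The scope is children entering by one of four triggers and one exploratory health outcome. Completion of the diagnostic evaluation, the primary outcome, is not affected.

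**What to change.** In Section 6.1.2, replace the descriptive comparison for LDL-C with follow-up LDL-C in a fixed window. Analyse it in a mixed model of the kind planned under Aim 2, in a form suited to a continuous outcome, with condition, calendar time and cluster. Adjust for:
- the last LDL-C before notification, defined the same way for all entrants, because MyCode and cascade entrants have no trigger LDL-C;
- trigger type, which deals with the shift in Step 3. To limit the shift in Step 4, split the LDL-C trigger by whether the test was a routine lipid profile at ages 9 to 11, if the EHR shows it.

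Report the share of entrants with a follow-up value by condition, so that differential capture is visible. Do not count any fall as a reduction. If a proportion is reported, state the percentage fall in advance and set it above within-person variation. In the working above, a 10% threshold still leaves 19% to 61% of untreated children counted, and a 30% threshold leaves 0% to 9%.

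The cost is analysis wording and slightly more work on EHR data. Some entrants will have no earlier LDL-C and need a stated rule, and the reported reduction may look smaller. Adjustment cannot repair follow-up that depends on unrecorded factors, so the result should still be read as exploratory.
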